## Abstract

**Background:**

Little is known about the efficacy and the working mechanisms of physical and occupational therapy interventions for children with cerebral palsy (CP). In recent years a shift from a child-focused intervention approach to a more context-focused intervention approach can be recognized. Until now the evidence on the efficacy and the working mechanisms of these interventions for children with CP is inconclusive. This study aims to evaluate the efficacy and working mechanisms of two intervention approaches compared to regular care intervention in improving mobility and self-care skills of children (2-3 years) with CP and their families: a child-focused intervention approach and a context-focused intervention approach.

**Methods/Design:**

A multi-centre, randomized controlled trial research design will be used. Ninety-four children with CP (Gross Motor Function Classification System (GMFCS) level I-IV; age 2 to 3 years), their parents, and service providers (physical and occupational therapists) will be included. During a period of six months children will receive child-focused, context-focused or regular care intervention. Therapists will be randomly assigned to deliver either a child-focused intervention approach, a context-focused intervention approach or regular care intervention. Children follow their therapist into the allocated intervention arm. After the six months study-intervention period, all participants return to regular care intervention. Outcomes will be evaluated at baseline, after six months and at a three months follow-up period. Primary outcome is the capability of functional skills in self-care and mobility, using the Functional Skills Scale of the Pediatric Evaluation of Disability Inventory (PEDI). Other outcomes will be quality of life and the domains of the International Classification of Functioning, Disability and Health - for Children and Youth (ICF-CY), including body function and structure, activities (gross motor capacity and performance of daily activities), social participation, environmental variables (family functioning, parental empowerment).

**Discussion:**

This paper presents the background information, design, description of interventions and protocol for this study on the efficacy and working mechanisms of child-focused intervention approach and context-focused intervention approach compared to regular care intervention in mobility and self-care skills of children (2-3 years) with CP.

**Trial registration:**

This study is registered in the Dutch Trial Register as NTR1900

## Background

The present paper describes the background and design of LEARN 2 MOVE 2-3 (L2M 2-3). This project is part of the Dutch national LEARN 2 MOVE research program, which evaluates interventions in rehabilitation for children and adolescents with Cerebral Palsy (CP) in different age cohorts [1-3].

For children with CP at young age in general a shift from a child-focused intervention approach to a more context-focused intervention approach can be recognized. Until now however, the evidence on the efficacy and the working mechanisms of these intervention approaches for children with CP are inconclusive. Moreover, it is not known which interventions are being used in clinical practice, and how these developments transfer into clinical practice. L2M 2-3 focuses on these questions.

The child-focused intervention approach and context-focused intervention approaches are based on different principles as can be described in terms of the International Classification of Functioning, Disability and Health (ICF;[4]) and the recently published derived version of it, the International Classification of Functioning, Disability and Health for Children and Youth (ICF-CY;[5]). In the ICF and ICF-CY a persons functioning can be described on various levels (Figure 1) in its relation with environmental and personal factors.

**Figure 1 F1:**
[figure not shown]
**ICF-model**.

Both the child-focused intervention approach and the context-focused intervention approach aim to improve activities and participation of the children. They differ however in the assumed pathways how to reach the goals at the level of activities and participation.

The child-focused intervention approach focuses primarily on remediation of *body function and structure *as the starting point of intervention. Interventions based on such an approach include: facilitation of normal movement patterns and postural control through physical handling [6-8], maintaining range of motion and joint alignment through stretching, casting and splinting [9,10], strength training [11-13], and treadmill training [14]. These strategies, focusing on remediation of body function and structure, can be performed in isolation or as part of practicing activities.

The context-focused intervention approach focuses primarily on changing constraints in the environment or task as the starting point of intervention. Both the physical environment and the social environment of the child are emphasized [15]. In the context-focused intervention approach the therapist will not elicit specific responses by handling the child, but will provide an environment that enables the child to learn to perform self-initiated actions within naturally occurring restraints. The child can then become an active problem solver throughout the day instead of being a passive recipient of treatment. The social context of the child, especially the family, plays an important role.

Currently, *CanChild *Centre for Childhood Disability Research in Canada is performing a study into the efficacy of a child-focused intervention approach compared to a context-focused intervention approach, the Focus on Function Study [16]. L2M 2-3 builds on the Focus on Function study in the way that the efficacy of the same child-focused intervention approach and context-focused intervention approach will be compared with the same outcome measures in different countries, and by adding the comparison with regular care. Little is known about the actual content of current interventions for young children with CP. They probably consist of a mix between the child-focused intervention approach and the context-focused intervention approach, without a clear theoretical base. To provide children with CP with the best intervention, it is necessary to understand which interventions are effective and why these interventions are effective.

The aim of the present project is to evaluate the efficacy of a child-focused intervention approach or a context-focused intervention approach versus regular care intervention in improving daily functioning of children (2-3 years) with CP and their families. In defining daily functioning it is important to distinguish three constructs of activity: capacity, capability, and performance. Capacity describes what a person can do in a standardized, controlled environment. Capability describes what a person can do in his/her daily environment. Performance describes what a person actually does do in his/her daily environment [17,18].

Primary outcome in the present study is the capability of functional skills in self-care and mobility, as reflected in the first research question. Other domains and concepts of the ICF-CY are secondary outcomes, leading to the following research questions. Which of the three intervention approaches results in:

i. greater achievement of capability in functional skills in mobility and self-care of the children?

ii. greater independence in the performance of mobility and self-care of the children?

iii. greater achievement of capacity of motor skills of the children in a standardized environment?

iv. greater participation of children and their families?

v. better quality of life of the children and their families?

In addition to the questions on efficacy, the working mechanisms of the child-focused intervention approach and the context-focused intervention approach will be examined. Parental stress, empowerment and family-centeredness of care will be analyzed in the three intervention groups. Moreover, variables that might be related to the efficacy of the intervention approaches and that might explain possible variability between children will be examined. In a longitudinal study of our research group on the development and determinants of daily activities in children with CP named PERRIN (Pediatric Rehabilitation Research in the Netherlands), and from recent literature, insight has been gained in child- and family-variables that possibly explain more about the working mechanisms of the interventions. These variables are: gross motor abilities [19,20], manual abilities [21,22], cognition of the child [21,23,24], and coping style of the parents [25-27]. We will collect data on these variables to get more insight in possible variability between children. Moreover, to get more insight into the working-mechanisms of the intervention approaches, part of the parents will be interviewed on their experiences with the interventions and therapists will be asked about preferences for intervention.

## Methods/Design

### Design

A multi-centre, randomized controlled trial research design will be used. The study protocol is approved by the Medical Ethics Committee of the University Medical Centre Utrecht, the Netherlands.

### Setting

The study is a multi centre study and will be conducted in approximately 15 rehabilitation centers in the Netherlands between September 2009 to December 2011.

### Study population

Ninety-four children with CP will be included. The inclusion criteria are:

- Children with diagnosis of CP [28];

- Children classified in Levels I-IV at the Gross Motor Function Classification System (GMFCS; [29,30]);

- Children enrolled in pediatric rehabilitation care, with at least physical or occupational therapy;

- Children receiving therapy with a frequency of at least three sessions per month;

- Children aged 24 months to 47 months (2-3 years) at the time of recruitment.

The exclusion criteria are:

- Children with planned surgery or medical changes during the study that may affect their motor function;

- Children whose families feel uncomfortable or unable to respond to interviews and questionnaires in Dutch (the language of all the study materials);

- Since this an efficacy study, parents who state that they will not be able to adhere to one or two of the intervention approaches or to the treatment schedule, will not be entered in the study.

Children and their parents will be approached by their treating pediatric physician. They will receive an information letter, an informed consent form, a brochure about the LEARN 2 MOVE 2-3 study, and a brochure about participating in scientific research. The researcher will contact the parents after two weeks to respond to possible queries and provide additional information when necessary. Children of parents who give informed consent will participate in the study.

### Sample size

Sample size was calculated for the Pediatric Evaluation of Disability Inventory (PEDI) (based on data from an earlier study [31]; with a subgroup analysis of children of 2-3 years) using the following assumptions in a one-way analysis of variance power analysis (based on a power of 80% and a two-sided α-value of 0.05). An estimated difference in the change scores between the context-focused intervention approach group and the regular care intervention group of 4.5 points (SD = 6.0) on the PEDI. Sigma for the three groups = 2.1. Taking into account the clustered nature of the sample of participating children a correction will be used, based on an average cluster size (number of children per therapist) of 2, and an ICC of 0.1. These specifications lead to a required total sample size of 85. Expecting a 10% drop-out in total 94 children will be recruited for the present study.

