### Study procedures

The three interventions arms will be distributed within a centre. The physical and occupational therapists who agreed to participate will be randomized in one of the three intervention arms by block randomization, with a block size of six. Children will follow their therapist into the intervention group that the therapist was assigned to. The therapist who provides the study intervention to the child will be the prime therapist for the children during the six months study-intervention period. Furthermore, the prime therapist is the one who will document on the session documentation, will set goals with parents and is the contact person for the researchers. The other therapists who treat the child will be available for expert information consultation. Therapists can participate in the study with a maximum of two children at the same time and with a maximum of four children overall in the study. We expect an average of two children per therapist.

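### The clustering allowance uses only the mean of two children per therapist, although up to four are allowed, so 85 children and 80% power are modestly optimistic

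*Protocol article*

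**What the plan says.** The Sample size section of the protocol article describes a "one-way analysis of variance power analysis (based on a power of 80% and a two-sided α-value of 0.05"). It assumes a difference in change scores between the context-focused group and the "regular care intervention group of 4.5 points (SD = 6.0) on the PEDI" and adds "Sigma for the three groups = 2.1". It then corrects for clustering "based on an average cluster size (number of children per therapist) of 2, and an ICC of 0.1", reports a required total of 85, and continues: "Expecting a 10% drop-out in total 94 children will be recruited for the present study".

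Under Study procedures, therapists are the randomised unit and children go with their therapist. A therapist may have a "maximum of two children at the same time and with a maximum of four children overall in the study". The same section adds: "We expect an average of two children per therapist". No distribution or coefficient of variation of cluster size is given, and no allowance for unequal sizes is mentioned.

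**The concern.** A correction built from the mean cluster size alone is exact only when all clusters have that size. With an average of two and a cap of four, any therapist who treats three or four children must be balanced by others who treat one. Larger clusters hold a disproportionate share of the children, so a typical child has more cluster-mates than the mean suggests, and the variance inflation is larger.

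The calculation leaves almost no room for this. It arrives at 84.8, rounded to 85, and recruits 94 where 85/0.9 = 94.4. Even a small understatement of the design effect therefore takes power below the stated 80%, and a non-significant result would be read against slightly more power than the design has.

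**Working it through.** **Inputs from the protocol article.** Three groups, alpha 0.05, power 80%, difference 4.5, SD 6.0, sigma of the group means 2.1, mean cluster size 2, ICC 0.1, cap of four children, 10% drop-out.

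**Inferred or assumed.** The factor 1.10 and a minimum of one child per therapist are not printed; they are inferred. The mix of cluster sizes is an assumption.

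**Step 1: recover the stated total.** Group means of 0, 0 and 4.5 have standard deviation 4.5 × √2/3 = 2.12, which matches the stated 2.1. So f² = (2.12/6.0)² = 0.125. For 80% power with 2 degrees of freedom, the large-sample (noncentral chi-square) non-centrality is 9.635. The base N is 9.635/0.125 = 77.08. With the factor 1 + (2 − 1) × 0.1 = 1.10, N = 84.8, the stated 85. (Using the rounded 2.1, f = 0.35 gives 78.65 × 1.10 = 86.5, within 3%.)

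**Step 2: design effect with unequal sizes.** DE = 1 + ((1 + CV²) × 2 − 1) × 0.1. At CV = 0 this is 1.10. It cannot be lower at this mean and ICC, and any spread raises it.

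**Step 3: thinning by drop-out.** The 85 are evaluable children. If each child is lost at random with probability 0.1, the expected number of remaining cluster-mates is multiplied by 0.9, so DE = 1 + 0.9 × ((1 + CV²) × 2 − 1) × 0.1.

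**Step 4: results**, all with mean 2 and the method of Step 1. Required N = 77.08 × DE. Power at 85 uses non-centrality 85 × 0.125/DE.

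| Assumed children per therapist | CV² | DE | Required N | Power at 85 | DE after thinning | Required N | Power at 85 |
|---|---|---|---|---|---|---|---|
| All 2 | 0 | 1.10 | 84.8 | 80.1% | 1.09 | 84.0 | 80.5% |
| 1, 2, 3 equally often | 0.17 | 1.133 | 87.4 | 78.8% | 1.12 | 86.3 | 79.3% |
| 1/2/3/4 in 40/30/20/10% | 0.25 | 1.15 | 88.6 | 78.2% | 1.135 | 87.5 | 78.8% |
| Two thirds 1, one third 4 (bound) | 0.50 | 1.20 | 92.5 | 76.3% | 1.18 | 91.0 | 77.1% |

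Example for the third row: the mean is 0.4 + 0.6 + 0.6 + 0.4 = 2.0 and the mean square is 0.4 + 1.2 + 1.8 + 1.6 = 5.0. So CV² = (5.0 − 4.0)/4.0 = 0.25 and DE = 1 + (2.5 − 1) × 0.1 = 1.15.

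**Step 5: keep the approximation apart.** With the exact noncentral F, power at 85 is 78.4% at the factor 1.10, before any spread in cluster size. That gap of 1.6 points to 80% (1.7 to the large-sample 80.1%) comes from the large-sample approximation, not from unequal clusters.

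**Step 6: drop-out.** 85/0.9 = 94.4 agrees with 94 to rounding.

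**The case against.** The strongest reply is that nothing has been miscalculated. The stated 85 follows from the stated inputs, and 94 follows from 85. Planning on a mean cluster size is a common simplification. The article says openly that it uses an average, and both sections give the same average, so they do not contradict each other. All of that stands.

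It is also fair that the bound is not a forecast. It needs two thirds of therapists with one child, one third with four and none in between, while the limit of two at a time means that four can be reached only by successive enrolment. Thinning recovers part of the loss, which leaves a shortfall of about one to three children for moderate mixes. An efficient mixed-model weighting would also trim the factors slightly, to 1.13, 1.14 and 1.18 before thinning.

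Finally, the ICC is itself uncertain by a similar amount. At ICC 0.05 the widest mix gives 1 + 2 × 0.05 = 1.10, and at 0.15 equal pairs already give 1.15. This limits the precision of any restated power. It does not make the minimum factor the natural planning value when the enrolment rule allows up to twice the mean.

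**Conclusion.** The point holds as a modest, conditional understatement. The plan uses the smallest design effect that its mean and ICC permit, while its enrolment rule allows clusters of different sizes. For moderate spread, about 86 to 89 evaluable children are needed instead of 85, or power at 85 is about 78 to 79% instead of 80%. At the bound under the cap of four, the figures are 91 to 93 children and 76 to 77%. These rest on the printed mean of 2 and ICC of 0.1, on an assumed size mix, and on random drop-out where thinning is counted.

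A reader might go further and infer that 85, 94 and 80% are established errors, or that unequal clusters alone bring power down to about 75%. The documents support neither. The stated totals reproduce, no size distribution is given, and figures that low arise only when the separate loss from the exact F-test is added in or the extreme mix is assumed.

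**What to change.** In the Sample size section, replace the equal-cluster correction by 1 + ((1 + CV²) × 2 − 1) × 0.1, and state the expected CV together with the distribution of one to four children per therapist behind it. Keep 94 recruited and report the power that this gives. With CV² = 0.25, for instance, the factor is 1.15 (1.135 if thinning is counted), and power at 85 evaluable children is 78.2% (78.8%) on the large-sample method. Name the method, so that the approximation is not confused with the clustering allowance.

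The cost is a reworded paragraph and a slightly less favourable stated power. The drop-out step, recruitment, design and analysis stay as they are.

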### Study procedures

The three interventions arms will be distributed within a centre. The physical and occupational therapists who agreed to participate will be randomized in one of the three intervention arms by block randomization, with a block size of six. Children will follow their therapist into the intervention group that the therapist was assigned to. The therapist who provides the study intervention to the child will be the prime therapist for the children during the six months study-intervention period. Furthermore, the prime therapist is the one who will document on the session documentation, will set goals with parents and is the contact person for the researchers. The other therapists who treat the child will be available for expert information consultation. Therapists can participate in the study with a maximum of two children at the same time and with a maximum of four children overall in the study. We expect an average of two children per therapist.

The study procedure for the participants is represented in Figure 2. After randomization procedures, therapists in the child-focused intervention approach and therapists in the context-focused intervention approach group will receive additional training. This training will start with both groups together (introduction and background of the study, and steps in discussing and formulating problems and goals with parents using the Canadian Occupational Performance Measure (COPM;[32]) and Goal Attainment Scaling (GAS;[33]). The second part of the training will be completed separately for each group and focuses on implementing the specific components of child-focused intervention approach or context-focused intervention approaches. Expert consultation will be available for therapists in each intervention group. The researchers and the consultant for each intervention will conduct the training sessions, providing both theoretical and applied information about the assessment and intervention protocols. Therapists will discuss case scenarios, and view videos of children. The training and training syllabus are developed based on materials from the Focus on Function study of *CanChild*. During the study therapists in the child-focused intervention approach and context-focused intervention approach groups will document sessions on standardized forms, and in the stage of goal-setting, will make a videotape of the child to make clear what the goals of the individual child and the parents are. The therapists will receive feedback on the session documentation and the video-tape which they send to the researchers. The therapists will have access to a consultant and the researchers, for support, problem solving, and resources. Therapists in the regular care intervention arm will be asked to work the way they are used to do, and at the end of the study their session documentation will be collected.

After inclusion in the study a baseline measurement (T0) will take place. Children will be assessed and parents will fill out questionnaires and will be interviewed on the measures as described in the Section Study Parameters. Parents can choose whether they would like to fill out the questionnaires on a digital or a paper version. Thereafter participants will follow their therapist into one of the three intervention groups for a six months study-intervention period. After these six months the second measurement (T1) will take place, after which all participants return to regular care intervention. At a three months follow-up period the third measurement (T2) will take place. Independent assessors who are blind for intervention allocation will asses the children and their parents.

**Figure 2 F2:**
[figure not shown]
**Design LEARN 2 MOVE 2-3 study**.

### Interventions

Children included in the study typically receive physiotherapy and/or occupational therapy with a frequency of at least three times a month. During the six months study-intervention period, all children will receive at least 18 sessions of intervention. The amount of intervention sessions will be documented in the session documentation of the therapists.

In the child-focused intervention approach and context-focused intervention approach the procedure of problem definition, priorities, goals, analysis, sub goals and evaluation will be the same as much as possible, to avoid a confounding effect by procedure (see Table 1).

**Table 1 T1:** Comparison of procedure of the child-focused, context-focused and regular care intervention

	Child-focused	Context-focused	Regular care
**Problem definition**	COPM	COPM	No instructions on documentation, therapists will document the way they are used to do. Documentation will be collected after the end of the study.
	
**Priorities**	COPM	COPM	
	
**Goals**	- Goal identification according to the COPM - Goals formulated SMART^1^	- Goal identification according to the COPM, with parents - Goals formulated SMART^1^	
	
**Analysis**	Arrange constraints and enablers in ICF-CY - focus on constraints and facilitators in the child	Arrange constraints and enablers in ICF-CY - focus on constraints and facilitators in the environment and the task	
	
**Sub-goals**	Sub-goals formulated SMART^1^	Sub-goals formulated SMART^1^, with parents	
	
**Intervention**	Focus on remediation of the child's abilities through changing the components of body function and structure	Focus on functional performance trough changing constraints in the task and/or the environment	
	
**Evaluation**	Therapist evaluate goal, when attained a new goal will be defined	Therapist evaluate with parents goal, when attained a new goal will be defined with parents	

^1^Specific Measurable Attainable Realistic Timely

To ensure that the procedures in the child-focused intervention approach and the context-focused intervention approach are the same, forms will be used to guide the steps.

